## Abstract

**Background:**

The highest incidence and prevalence of mental health problems across the lifespan as well as the first onset of most long-term mental health conditions are reported for youths between 14 and 25 years of age. At the same time, only 25% of adolescents with mental health problems receive professional treatment. One explanation for poor treatment access in youths is their low help-seeking behavior. Barriers that can keep children and adolescents (C&A) from seeking professional help include a lack of perceived need, structural barriers, or stigma. Interventions based on e-technology might present an effective approach, overcoming these barriers by reducing stigma and providing low-threshold access with enhanced reach, ultimately facilitating help-seeking for mental health problems among youths.

**Methods:**

The study is designed as a multi-center, randomized controlled trial. In total, an estimated number of *n* = 1,500 C&A with mental health problems, drawn from a school-based sample of *n* = 15,000 pupils attending school grades 6 to 13 (≥ 12 years of age), recruited in five regions of Germany, will be randomized either to an intervention (ProHEAD online) or a control condition. C&A in the intervention group will receive online access to tailored information and individual advice on where to seek professional help for their specific needs close to their place of living, case reports of and interaction with peers, as well as the opportunity for online and telephone counseling. C&A in the control intervention will receive a recommendation to seek help and online information on where to find professional help. All participants will be asked to complete questionnaires concerning their help-seeking behavior at baseline, during the intervention (monitoring), and also at a 1 and 2 year follow-up. The primary endpoint is the number of C&A seeking conventional face-to-face professional help in the real-world setting within 1 year after their initial screening.

**Discussion:**

The trial will investigate if an Internet-based intervention can increase professional help-seeking in C&A with mental health problems. With its randomized controlled design and large-scale school-based sampling, the study aims to overcome the shortages of previous research. The intervention has the potential to narrow the treatment gap in C&A and to ultimately improve the mental health care system.

**Trial registration:**

German Clinical Trials Register, DRKS00014685. Registered on 7 July, 2018.

**Electronic supplementary material:**

The online version of this article (10.1186/s13063-018-3157-7) contains supplementary material, which is available to authorized users.

## Background

Children and adolescents (C&A) are frequently affected by psychiatric illness and mental health problems. Recent population-based studies report a 50% incidence of mental health problems in the age group between 12 and 25 years, and a 12-month prevalence of 40% for those between 13 and 18 years of age [1]. Mental health problems in this age group are associated with a high risk of persistence and serious functional impairment, emphasizing their long-term impact [2]. A recent review reported that neuropsychiatric disorders are the most common causes of disability (45%) in individuals between 10 to 24 years of age [3]. In sum, the highest incidence and prevalence of mental health problems across the lifespan and the first onset of most long-term mental health conditions are reported for youth between 14 and 25 years of age [4].

At the same time, and most alarmingly, youths clearly show the worst service access [4]. There is evidence that only 20–40% of adolescents with mental health problems are actually detected by health services and only 25% receive appropriate professional treatment [5]. This problem has been repeatedly confirmed for a variety of highly prevalent mental health problems such as depression [6], eating disorders [7], and substance misuse [8]. A representative study throughout Europe that included a school-based screening of *n* = 13,070 C&A (13–17 years of age) showed that at least 12.5% were in need of mental health care. However, less than one third took the offer of receiving direct professional help [9], illustrating very low help-seeking behavior among European adolescents at risk. These data fit those of previous studies concluding that C&A with mental health problems often do not receive treatment due to low help-seeking behavior [10, 11]. This is highly worrying, as the group of older C&A (aged 12–17) can be seen as the most important target group for early detection of individuals with mental health problems. Early detection increases the chance of early treatment, thus diminishing the risk of recurrence and/or serious residual damage, and thereby providing an opportunity to improve psychosocial outcomes and reduce health economic costs [12, 13].

Several barriers have been identified that potentially keep C&A from accessing mental health services [14]. A lack of perceived need for services, preference for self-management, fear of hospitalization, a lack of service availability within a reasonable time, lack of information, and structural factors (e.g., distance, finances) have been identified as key barriers to care [15]. Key components of C&A-friendly services (according to the World Health Organization) are availability, easy accessibility, equitability (e.g., being non-judgmental; open for all young people regardless of gender, culture, marital status, socioeconomic status, etc.), acceptability (e.g., having clear policies about confidential and patient-centered care), and appropriateness (e.g., staffed by skilled clinicians) [16].

By combining these features, interventions based on e-technology might present an effective approach to overcome barriers of help-seeking and to facilitate access to conventional care. Over the past decade, technology has played an increasingly bigger role in the delivery of psychosocial and psychotherapeutic interventions (“e-mental health”). E-mental health and Internet-based interventions have the advantage of easy, low-threshold access, enhanced reach, including traditionally underserved populations, relatively low cost, and time efficiency. In addition, technology allows for providing flexible interventions that are tailored to the individual needs and preferences of participants. Across the spectrum of mental health problems, growing evidence points to the potential of e-interventions for prevention, self-help treatment, counseling, and relapse prevention, and also as an adjunct to conventional psychotherapy using various forms of media and technology [17, 18]. It is assumed that Internet-based interventions may improve mental health literacy and contribute to a de-stigmatization of mental illness, thus promoting help-seeking attitudes, intentions, and ultimately behaviors [19]. However, only a few studies attempted to utilize Internet-based interventions to promote mental help-seeking. A recent review identified 18 studies, all with major methodological limitations (i.e., small sample sizes, lack of control group, no follow-up, and failure to assess behavioral outcomes) [20]. Furthermore, existing Internet-based interventions mostly address one particular health condition (mainly depression or anxiety), rather than providing different modules for a broad range of mental health problems prevalent in C&A all integrated in one superordinate program. Promoting Help-seeking using E-technology for ADolescents (ProHEAD) is such a superordinate program, which covers mental health problems (i.e., conduct problems, hyperactivity/inattention, peer relationship problems, emotional problems, eating disorders, addiction, and suicidality) not jointly covered by other programs. Finally, previous research is limited by the fact that the interventions aiming to improve help-seeking have almost exclusively consisted of one-time, fully automated tools (mostly psychoeducational content), not giving consideration to the heterogeneous and complex pathways to care [15]. By specifically addressing these methodological issues, an intervention based on e-technology bears great potential to conquer various barriers of help-seeking in C&A, to facilitate service access, and to finally contribute to relieve the burden of mental disease in youths.

## Objectives

The aim of the present study is to develop, implement, and evaluate an Internet-based program to promote help-seeking in C&A with mental health problems (i.e., scoring above critical thresholds in validated self-report questionnaires on diverse emotional and behavioral problems) across all disorders in a randomized controlled trial (RCT). The program will make use of this age group’s familiarity with the Internet to provide a low-threshold access to mental health assistance.

## Hypotheses

The primary hypothesis is that a greater proportion of C&A with mental health problems who are randomized (intention-to-treat) to help-seeking assistance through an individualized online based intervention are more likely to actually utilize professional (formal) face-to-face mental health care from a child and adolescent psychiatrist or psychotherapist within 1 year (primary endpoint), compared to a control group receiving information only. Secondary hypotheses are that C&A allocated to the intervention group will score more favorably on measures of mental health problems, health-risk behaviors, and quality of life in the respective follow-up assessments, compared to the control group. Additionally, health economic analyses will be conducted to assess economic aspects of the newly developed intervention.

## Methods/design

### Setting and recruitment

The trial is part of a multi-center consortium situated at six study sites across Germany and led by the managing site at the Clinic of Child and Adolescent Psychiatry at the University Hospital of Heidelberg (for details on the consortium, see the Editorial “*Promoting Help-seeking using E-Technology for ADolescents: The ProHEAD Consortium*”). The study protocol was approved by the Ethics Committee of the Medical Faculty at the University of Heidelberg.

A school-based sample of *n* = 15,000 C&A in grades 6–13 (≥ 12 years of age) will be recruited at five regions in Germany (Hamburg, Heidelberg, Leipzig, Marburg, Schwäbisch Gmünd). Permission to contact schools within the regional districts of all five recruiting sites will be requested from federal authorities. A complete list of schools in regional districts will be acquired. Schools are randomly selected for each school type separately to ensure a random selection of schools that ultimately represents the distribution of school types within the recruitment area. The school list is stratified by regional district^1^ and school-type.^2^ Within these strata the order of schools is random. Regarding the intervention, individual-level randomization is performed on all eligible participants to ensure timely allocation to one treatment arm. Schools of the respective school types will be contacted and informed about the possibility of participating in the trial in random order, until the prospected sample size by site is reached. Eligible C&A (≥ 12 years of age, sufficient German language skills, access to the Internet) and their legal guardians are asked to provide written informed consent and participate in a school-based screening covering various forms of mental health problems (detailed subsequently).^3^ Study personnel will check back on the return of the written informed consent sheets a couple of weeks after an informative class meeting and the distribution of study information materials. On the day of the assessment, C&A will further receive an emergency contact card, detailing procedures in the case of emergency or urgent request for professional consultation. School-based assessments will be repeated after 12 and 24 months.

Based on the screening results, each participant will be allocated to one of the five Internet-based trials (general mental health problems [this RCT]; eating disorder symptoms [21]; risky alcohol use [22]; depressive symptoms [23]; no mental health problems [24]). C&A meeting inclusion criteria for more than one RCT will be randomly allocated to one of the RCTs. Criteria for the allocation of participants to the five individual ProHEAD RCTs are based on the latest scientific evidence from epidemiological studies. However, this is the first time that the overall algorithm is applied on a consortium-wide basis simultaneously screening for various mental health problems. Therefore, a preliminary data analysis will be conducted following completion of 10% of the screening assessments (*n* = 1,500) in order to determine the actual allocation ratio to the five ProHEAD trials and to adjust the screening algorithm if necessary.

### Inclusion and exclusion criteria

C&A from the school-based sample (≥ 12 years of age, sufficient German language skills, access to the Internet) are included in the present clinical trial if they endorse any form of mental health problems, including serious suicide thoughts or attempts in the past 2 weeks, a score above 19 points on the Strengths and Difficulties Questionnaire [25] total score, or a score above the defined thresholds for one of its sub-scales: *emotional symptoms* (scores > 6), *conduct problems* (scores > 4), *hyperactivity/inattention* (scores > 6), or *peer relationship problems* (scores > 5). Further, C&A will be included if they report the following: body mass index (BMI) < 5th percentile (adjusted for age and gender) AND concurrent fear of weight gain OR daily binge eating OR daily vomiting OR current alcohol use disorder [26] OR a score above 9 on the Patient Health Questionnaire-9 modified for adolescents (PHQ-A) [27]. C&A scoring below all clinical cut-offs are allocated to other trials nested within the ProHEAD Consortium. C&A not providing written informed consent (including parental consent) will be excluded.

### Randomization and blinding

For the current trial, eligible C&A will be randomized to one of the two treatment arms based on a permuted block design (Fig. 1). Randomization will be automatically performed via a predefined algorithm after the school-based screening on an individual subject level to ensure timely allocation and allocation concealment. Participating C&A will receive an email with a link to activate their personal account in the allocated group. Participants cannot be blinded due to the different natures of the interventions. Blinding of the researchers is non-applicable. The data analysts will be blinded to group allocation (dummy coded) when conducting the statistical analyses.

**Fig. 1 Fig1:**
[figure not shown]
ProHEAD online trial flow. *SEED* Short Evaluation of Eating Disorders, *AUDIT* Alcohol Use Disorders Identification Test, *PHQ-A* Patient Health Questionnaire-9 modified for adolescents, *SDQ* Strengths and Difficulties Questionnaire, *C&A* Children and adolescents

### Sample size

Based on the expected sample size to be allocated by randomization (*n* = 1,500), a power analysis for the trial revealed that the study is powered to detect small effects (1.13 ratio, i.e., 13% differences in help-seeking between groups, alpha = 5%), assuming a critical χ^2^ = 34.55. All tests will be two-sided.

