### Statistical analysis

The main hypothesis is that a greater proportion of those C&A with mental health problems who are randomized to ProHEAD online (intention-to-treat) will present themselves within the conventional professional mental health care system after 1 year compared to C&A in the control condition. This will be addressed using chi-squared tests with Fisher’s exact *F* to adjust for zero inflation of cell distribution sizes (C&A who utilized professional help versus C&A who did not utilize professional help) on group differences. In secondary analyses, predictors of help-seeking behavior (i.e., sex, age, utilization of the online intervention, and symptom severity at initial school-based screening) will be assessed using multinomial logistic regression analyses. Engagement time per participant (minutes per day, days per month) and content of engagement will be tracked to get a reliable estimate of the utilization of the platform that is of interest for analyses of the dose-response relationship. Missing data and subjects withdrawn from the trial will be handled using an intention-to-treat approach. All subjects randomized will be considered in the analyses. In the case of drop-outs or missing data, it will be assumed that these C&A did not present themselves within the mental health care system to provide a conservative estimate of the true effect. Potential class and school effects will be tested and adjusted for if necessary.

In addition, a cost-effectiveness analysis, including the calculation of the incremental cost-effectiveness ratio (ICER), will be conducted. To provide information on cost per quality-adjusted life year (QALY), cost-utility analyses will be used.

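### The power statement is wrong as written: a critical chi-squared of 34.55 cannot belong to a two-arm, two-outcome test, and the scale of the 1.13 / 13% effect is left undefined

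*Protocol article*

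**What the plan says.** The Sample size section of the protocol article is a short power claim. It starts from the number of pupils that screening is expected to yield: "Based on the expected sample size to be allocated by randomization (*n* = 1,500"). It then says that "the study is powered to detect small effects (1.13 ratio, i.e., 13% differences in help-seeking between groups, alpha = 5" per cent), "assuming a critical χ^2^ = 34.55". It closes with "All tests will be two-sided".

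Three other places bear on this.
- Randomization and blinding gives two arms. Statistical analysis gives a chi-squared/Fisher comparison of pupils who did and did not use professional help.
- The Background supplies the only relevant rates in the article. Of adolescents with mental health problems, "only 25% receive appropriate professional treatment", and 20–40% are detected by services. In a European school screening study, under a third of those in need accepted direct help.
- For drop-outs and missing outcomes, Statistical analysis says that "it will be assumed that these C&A did not present themselves within the mental health care system".

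**The concern.** Two arms by two outcome categories is a 2×2 table with 1 degree of freedom. A critical value of 34.55 is about nine times too large for that test at 5%, so the printed calculation does not describe the planned analysis.

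The effect size cannot be pinned down either. A ratio of 1.13 on a rate of 25% is a difference of 3.25 percentage points. A 13-point difference is four times as large. The trial's power is very different in the two cases, and the sentence does not say which is meant.

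What is at stake is how a null result would be read. A reader told that small effects were detectable would take it as evidence against a ratio of 1.13, when the trial may have had little chance of showing one.

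**Working it through.** **Inputs from the article.** Total 1,500, alpha 5%, two-sided, ratio 1.13 or 13% (Sample size); two arms (Randomization and blinding); two outcome categories (Statistical analysis); rates of 20% to 40% (Background, used for illustration only).

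**Assumptions added here.** 1:1 allocation, hence 750 per arm, and 80% as the reference power.

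**Step 1: the printed critical value.** Degrees of freedom = (2 − 1) × (2 − 1) = 1. The upper 5% point of chi-squared on 1 df is 3.84. A value of 34.55 on 1 df has p = 4.2 × 10⁻⁹. At alpha 5% the value for 22 df is 33.92 and for 23 df is 35.17, so 34.55 falls between them and fits no integer df. The plan's figure cannot be reproduced. Taken literally as the cut-off, it would leave essentially no power for 25% vs 28.25%, and about 32% even for 25% vs 38%.

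**Step 2: effect read as a ratio of 1.13.** For the two-proportion test with pooled variance under the null (equivalent to the 1-df chi-squared), and p̄ the mean of p₁ and p₂:

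power = Φ{ [ |p₂ − p₁| − 1.96·√(2p̄(1 − p̄)/n) ] / √( [p₁(1 − p₁) + p₂(1 − p₂)]/n ) }

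At a control rate of 25%: p₁ = 0.25, p₂ = 1.13 × 0.25 = 0.2825, p̄ = 0.26625, n = 750. The null standard error is 0.02282 and the alternative standard error is 0.02281. So (0.0325 − 1.96 × 0.02282)/0.02281 = −0.54, and power = Φ(−0.54) = 0.296 with unrounded inputs.

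| Control rate | Rate at ratio 1.13 | Difference (points) | Power, 750 per arm | Total N for 80% | Detectable at 80%, 750 per arm |
|---|---|---|---|---|---|
| 20% | 22.6% | 2.6 | 23% | 7,784 | 6.1 points, ratio 1.30 |
| 25% | 28.25% | 3.25 | 30% | 5,806 | 6.5 points, ratio 1.26 |
| 33.3% | 37.7% | 4.3 | 42% | 3,826 | 7.0 points, ratio 1.21 |
| 40% | 45.2% | 5.2 | 53% | 2,838 | 7.2 points, ratio 1.18 |

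Power of 80% for a ratio of 1.13 is reached at a control rate of about 55%.

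Other conventions do not rescue the figure at these rates. Read as an odds ratio of 1.13, power is 16% to 21%. One-sided testing, which the article rules out, gives 34% to 65%. Allocation of 2:1 or 1:2 gives 26% to 27% at 25% and 38% at 33.3%.

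**Step 3: effect read as 13 percentage points.** At 25% vs 38%, 33.3% vs 46.3% and 40% vs 53%, power with 750 per arm exceeds 99.9%. The ratio is 0.38/0.25 = 1.52 at 25% and 1.39 at 33.3%. The two descriptions agree only if 0.13 × control rate = 0.13, that is, at a control rate of 100%.

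**Step 4: missing outcomes.** If a fraction m is missing equally in both arms and counted as no help sought, both rates are multiplied by (1 − m) and the ratio is unchanged. For illustration, m = 20% (an assumption; the article gives no attrition figure) turns 25% vs 28.25% into 20% vs 22.6%. That is the first row of the table, with 23% power.

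**The case against.** Several points on the other side are fair.

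- **The two expressions need not conflict.** A ratio of 1.13 is a 13% relative difference. A reader might infer that the article falsely equates a ratio with a difference in proportions, but it never mentions percentage points. This stands: the fault is an unstated scale, not a false equation.
- **The Background rates are not design assumptions.** They come from cited studies and measure something else. The control-arm endpoint is self-reported use of professional care over a year, after pupils have received their results, advice and local addresses. This also stands, so the shortfall in Step 2 is conditional. It does hold for every control rate below about 55%, and nothing in the article points to a rate that high.
- **An article may leave the control rate and power to a fuller document.** Agreed, and their absence is not the point. The point is a printed critical value that does not fit the test, and an effect that cannot be interpreted.
- **The number 34.55 changes nothing in the conduct of the trial.** A reader might infer that significance would be judged against it. The documents do not support that: the analysis is an ordinary chi-squared/Fisher test at 5%. It is a reporting error, but in the sentence that carries the power claim.
- **Small effects can be detected in the standardised sense.** With w = 0.10 the noncentrality is 1,500 × 0.10² = 15, and power is 97%. True, but the article defines its small effect as 1.13 / 13%, and at a control rate of 25% a ratio of 1.13 is far smaller than that.

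**Conclusion.** The power statement is wrong as written. The critical value is wrong without any assumption about rates: it should be 3.84 on 1 df. The effect size is ambiguous, and the ambiguity decides the conclusion. As a ratio of 1.13, power is about 23% to 53% over control rates of 20% to 40%. As 13 points, it is above 99.9%, but the effect is then not a ratio of 1.13.

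These power figures rest on 1:1 allocation and on background rates used as a plausible range. A reader might go further and conclude that the trial is underpowered outright. The documents do not support that, because they declare no control rate and one reading leaves ample power. What they do support is that, on the reading that fits the word ratio, the claim fails at every rate the article cites. The rule for missing outcomes lowers power further for a given ratio.

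**What to change.** Reword the Sample size section and leave the 1,500 pupils unchanged.

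1. Replace 34.55 with 3.84 (1 df).
2. State whether the effect is a risk ratio, an odds ratio or a difference in percentage points.
3. State the control rate, power and allocation ratio actually used.
4. Restate the detectable effect to match. For example, with 750 per arm and 80% power it would be about 6 to 7 percentage points: a ratio of about 1.30, 1.26 or 1.21 at control rates of 20%, 25% or 33%.
5. Add a sentence saying that counting missing outcomes as no help sought lowers both observed rates, and show the detectable effect at the attrition the investigators expect.

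No extra pupils and no change of analysis are needed. The cost is that, on the ratio reading, the stated detectable effect becomes less favourable.
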